## 6.6 Treatment Discontinuation

Subjects will be free to discontinue treatment or withdraw from the study at any time, for any reason, or they may be withdrawn/ removed if necessary in order to protect their health (see reasons for withdrawal below).

Patients will be removed from further treatment for the following reasons:

- Disease Progression
- Non-compliance with study procedures
- Subject no longer consents to participate in the study
- Intercurrent illness that interferes with study assessments
- Treatment-related toxicity requiring treatment discontinuation
- Incidence or severity of AEs that indicates a potential health hazard to the subject
- For the fourth occurrence of the same Grade  $\geq 3$  non-hematological toxicity
- A delay in treatment > 21 days unless approved by the Lead Principal Investigator, or due to congestive heart failure unresolved for > 28 days the treatment shall be discontinued ([see Table 6-8](#))
- Treating investigator discretion
- Requirement for alternative therapy
- Suspected or positive pregnancy
- Termination of the study by the sponsor

The Lead Principal Investigator should be contacted regarding any impending discontinuation of a study subject. If the reason for withdrawal is the occurrence of an AE, the subject will be followed until such events resolve, stabilize, and, according to the treating investigator's judgment, there is no need for further follow up. The reason for withdrawal from study must be documented in the case report form.

Any Grade 5 toxicity related to study treatment will prompt stopping of the trial until further review is completed. Additionally, development of Grade 4 of non-hematologic toxicities in 2 or more patients will prompt the DSMB to stop the study for review to determine whether the trial should be terminated due to excessive toxicity.

In case of premature discontinuation of the study treatment, the investigations scheduled for the EOT should be performed, if possible. Should a patient decide to withdraw, every effort will be made to complete and report the observations as thoroughly as possible. The treating investigator should contact the patient to determine as completely as possible the reason for the withdrawal. A complete final evaluation at the time of the patient's withdrawal should be made, with an explanation of why the patient is withdrawing from the study.

### **6.6.1 Duration of Follow Up**

Long-term follow up will include an assessment for disease progression in subjects who did not progress during treatment. This should occur every 3 months (+/- 30 days) for 5 years from safety follow-up visit (28 days post-last study treatment). Subjects who do progress will be followed for survival for 2 years from the completion of the safety follow-up visit or until death, whichever occurs first. This should occur every 3 months (+/- 30 days) and can be done over the phone.

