| Duration of Treatment            | 
The total study enrollment period is expected to be 12-18 months. A subject is considered to have completed the treatment phase of the study 4 weeks (28 days) after the end of the last treatment cycle. Excluding long-term follow-up, the treatment phase of the study will be completed once the last subject completes treatment the 28-day safety follow-up visit. Subjects who have not progressed will be followed for progression for up to 2 years from the first patient enrollment.
                                                                                                                                                                                                                                                                                                                                                                                                                                                                                                                                                                                                                                                                                                                                                                                     |

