### **2.2 Secondary Objectives**

Secondary objectives include characterization of efficacy variables:

- Rate of MRD by next generation gene sequencing (NGS) by clonoSEQ® (Adaptive Biotechnologies) at the end of Cycle 8 and at the end of Cycle 24, and then yearly for as long as no PD up to 2 years.
- Duration of response (DOR), progression free survival (PFS), time to progression (TTP), and overall survival (OS).
- Overall response rate defined as partial response or better (>PR) including the rate of VGPR or better (>VGPR) and near-complete response or better (sCR/CR/nCR) across entire treatment in high-risk and low-risk patients at indicated time points and as best response.
- Safety and tolerability of combination of D-KRd.

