## 6 TREATMENT PLAN

Please refer to the study calendar ([Appendix 8](#)) for an overview.

After screening, eligibility determination and enrollment, subjects will receive daratumumab, carfilzomib, lenalidomide, and dexamethasone, in 28-day cycles until progression, unacceptable toxicity or subject withdraws consent. The total study enrollment period is expected to be 12-18 months. A subject is considered to have completed the treatment phase of the study 4 weeks (28 days) after the end of the last treatment cycle. Excluding long-term follow up, the treatment phase of the study will be completed once the last subject completes the 28-day safety follow-up visit. Subjects who have not progressed will be followed for progression for up to 2 years from the completion of the safety follow-up visit. Subjects who have progressed, or have been removed from treatment for another reason, will be followed for survival for up to 2 years from the completion of the safety follow-up visit. An attempt will also be made to follow ASCT subjects for progression.

A subject is considered to be off-treatment following a 28-day safety follow-up period after the last treatment. Long-term follow-up for survival will be 2 years from the end-of-treatment visit.

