### **10.2.3 Secondary Endpoint Analysis**

The rate of MRD-negative disease by NGS will be reported at screening, 8, 12, 18, 24 months and then yearly until progression up to 5 years. Additionally, sites will be required to provide unstained pre-treatment slides to assess MRD by Adaptive. Comparison between D+KRd and historical KRd+ASCT rates will be made using a standard chi-square or Fisher's exact test. At the conclusion of the trial, with all subjects evaluated for PFS assessment at 5-years, the rate of MRD-negative status will be compared between D+KRd and historical KRd+ASCT data. This analysis will be conducted by contingency tables, or by adjusted logistic regression models, which will explore for any important confounders. Improvement of response during therapy measured at 6 and 12 months first treatment on protocol will be compared between D+KRd and historical KRd+ASCT data. Proportions of improving patients will be reported by treatment group, and comparisons of those proportions will be conducted using the chi-square or Fisher's exact tests. Overall survival will be calculated from date of first treatment on protocol until death from any cause and measured based upon the intention-to-treat paradigm, and will be compared between D+KRd and historical KRd+ASCT data using Kaplan and Meier survival models and the log-rank test statistic. In addition, all secondary endpoints will be tested for differences to historical controls using the one-sample log-rank test. The duration of MRD-negative disease will be calculated between the date of first occurrence of MRD-negative status, until such time as MRD-positive disease assessment or date of disease progression. Comparisons of duration of MRD-negative status may require the use of interval censoring methods. And finally, safety of the regimens will be assessed by comparing CTCAE Grade toxicity occurrence between D+KRd and historical KRd+ASCT data. Toxicity of Grade 2 and higher will be tabulated for each system organ class (SOC) and common individual toxicities occurring with SOC's reported. The maximum graded toxicity overall and within SOC will be reported per patient with the results summarized by treatment group and frequencies compared using chi-square tests or Fisher's exact tests as appropriate.

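### Follow-up horizons contradict each other and Section 10.2.3: depending on the section that governs, either the 5-year analyses have no data or overall survival is censored according to progression

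*Protocol*

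**What the plan says.** **Progression follow-up in patients who have not progressed.**
- Section 6.6.1: "This should occur every 3 months (+/- 30 days) for 5 years from safety follow-up visit". Appendix 8, footnote 23, repeats the 5 years.
- Section 6: "Subjects who have not progressed will be followed for progression for up to 2 years from the completion of the safety follow-up visit". Section 6.1.3 also gives 2 years, for survival and progression together, after stopping for any reason.
- Synopsis, Duration of Treatment: "Subjects who have not progressed will be followed for progression for up to 2 years from the first patient enrollment".

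**Survival follow-up.**
- Section 6.6.1: "Subjects who do progress will be followed for survival for 2 years from the completion of the safety follow-up visit or until death".
- Section 4.1.4 applies the same 2 years to those who progress during treatment. It has patients in general contacted every 3 months for both outcomes and refers to 6.6.1 for the duration.
- Section 6: "Subjects who have progressed, or have been removed from treatment for another reason, will be followed for survival for up to 2 years".
- The Appendix 8 footnote on survival and new cancers (28 in the list) gives contact at least every 3 months, with no end date and no split by progression.

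**MRD sampling.**
- Section 2.2: "then yearly for as long as no PD up to 2 years". Section 7 and the Appendix 8 MRD footnote (31 in the list) also stop 2 years after end of treatment.
- Section 4.1 continues to 5 years in ongoing sCR, counted from a randomization that this trial does not have.

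**Planned analyses, Section 10.2.3.** The MRD comparison at the close of the trial is made "with all subjects evaluated for PFS assessment at 5-years". MRD rates are reported yearly up to 5 years. OS runs from first treatment and is compared with historical KRd+ASCT by Kaplan-Meier and log-rank.

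**The concern.** All of this is current text, so a site cannot tell from the protocol when to stop contacting a patient. How long patients are followed decides which data exist, and no later analysis plan can recover deaths or progressions that were never collected.

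Two different things can go wrong. If the 2-year sections are followed, the 5-year PFS and MRD statements in 10.2.3 have nothing behind them. If 6.6.1 is followed, progressors leave survival follow-up years before the others. Kaplan-Meier and log-rank assume that a patient censored at a given time has the same outlook as those still observed. Progression predicts death, so that assumption fails, OS is overstated, and the overstated curve is then set against historical KRd+ASCT.

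**Working it through.** The protocol ties no sample size, power or event count to follow-up, so it has no figure of its own to reproduce. Two checks apply.

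**1. Calendar, counted from first treatment.** Inputs: 28-day cycles and 24 cycles (4.1.2.1, synopsis), a safety visit 28 days after the last dose (4.1.3, 6.6.1), and the caps quoted above. End of treatment is taken as the end of Cycle 24, as the Appendix 8 MRD footnote does.
- 24 × 28 = 672 days = 22.1 months. Adding 28 days (0.9 months) puts the safety visit at 23.0 months.
- Non-progressing completer under Sections 6 and 6.1.3: 23.0 + 24 = 47.0 months.
- The same patient under 6.6.1 and footnote 23: 23.0 + 60 = 83.0 months.
- Survival follow-up after progression at month 6: 6 + 0.9 + 24 = 30.9 months; at month 12: 36.9 months.
- Last MRD sample at 2 years after end of treatment: 22.1 + 24 = about 46 months, or 47 if counted from the end-of-treatment visit.
- Synopsis rule with 12 to 18 months of accrual: the last patient has 24 − 18 = 6 to 24 − 12 = 12 months, less than the 22.1 months that treatment takes.

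So under the 2-year sections nobody who ends treatment by Cycle 24 reaches 60 months.

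**2. Effect on Kaplan-Meier OS.** Large-sample simulation with exponential times.
- From the protocol: 4-year PFS of 69% with KRd (Section 1.7), giving a progression hazard of −ln(0.69)/4 = 0.0928 per year.
- Assumed, not in the documents: death without progression at 1% a year, added on top, and median post-progression survival of 2, 3 or 4 years.

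5-year OS in percent, with the excess over the true value:

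| Median post-progression survival | True | Only on-treatment progressors stop at 2 years (4.1.4 wording) | Literal 6.6.1: any progressor stops at safety visit + 2 years, or at progression if later |
|---|---|---|---|
| 2 years | 75.9 | 78.8 (+2.9) | 83.2 (+7.3) |
| 3 years | 80.3 | 83.0 (+2.7) | 86.4 (+6.1) |
| 4 years | 83.2 | 85.6 (+2.4) | 88.4 (+5.2) |

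A second simulation widened the post-progression median to 1 to 4 years and set the hazard of death without progression at 0 or 0.001 per month. The excess was then 1.9 to 3.1 points on the 4.1.4 wording and 4.5 to 8.6 points on the literal one.

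Under a uniform 2-year cap the curve ends near 47 months. At 3.9 years it is still 1.2 to 1.6 points too high, because the safety visit comes earlier for those who progress. With 5 years of survival follow-up from the safety visit for every patient, the simulation recovers the true 5-year OS.

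**The case against.** The strongest reply is that the two failures belong to different readings. If 6.6.1 and footnote 23 govern, patients who did not progress on treatment are assessed for 5 years and the others already have their PFS event, so 5-year PFS data exist. If the 2-year sections govern, the length of follow-up after the safety visit no longer depends on progression and the OS bias shrinks to 1 to 2 points. That is correct: a reader might infer both a large OS bias and missing 5-year PFS data, but no single reading gives both.

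The literal reading of 6.6.1 is also the harshest. Section 4.1.4 limits the 2-year stop to progression during treatment, and the Appendix 8 survival footnote has no end date. Hence 5 to 7 points is a worst case. No 5-year OS estimate is explicitly planned either. With 45 patients the standard error of an OS near 80% is √(0.8 × 0.2 / 45) = 6.0 points even with complete follow-up, about twice the milder bias. That limits the weight of the point, but imprecision does not remove a bias of known direction.

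A reader might further infer from Section 6 that patients stopped for toxicity or transplant are followed for survival only, so that PFS is censored at stopping. The documents do not support this. Section 6.1.3 gives 2 years of progression follow-up after stopping for any reason. Sections 4.1.4 and 6.6.1 cover anyone who did not progress on treatment, and Section 6 itself follows those who have not progressed. Nor is it settled that MRD sampling ends at 2 years, since Section 4.1 continues it in ongoing sCR. That is a contradiction to resolve.

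What stands is the conflict between sections, the mismatch with 10.2.3, and survival follow-up that depends on progression in 6.6.1 and 4.1.4.

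**Conclusion.** The point holds and should be corrected.
- **If the 2-year sections govern:** follow-up ends at about 47 months for a 24-cycle completer, and the 5-year PFS and MRD analyses cannot be done. This takes end of treatment as the end of Cycle 24. If the later single-agent lenalidomide counts as study treatment, the safety visit moves later.
- **If 6.6.1 governs:** 5-year PFS is available, but OS is biased upward by about 2 to 3 points at 5 years on the milder reading and 5 to 7 points at worst.
- **MRD:** under the 2-year sampling rule there are no samples to match the 5-year reporting. Under Section 4.1 there are samples only in patients with ongoing sCR.

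The sizes rest on the assumed post-progression survival and death rates. The direction needs only that death is likelier after progression than before it. The primary binomial test at the end of Cycle 8 is unaffected. This is a matter for secondary endpoints and for conduct at the sites.

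**What to change.** 1. State one follow-up rule, in the same words, in the synopsis and Sections 4.1, 4.1.4, 6, 6.1.3, 6.6.1 and Appendix 8.
2. Follow every patient for survival to the same horizon, whatever the progression status or reason for stopping. Follow every patient without progression for progression to that horizon.
3. The horizon must reach at least 5 years from first dose. It need not shorten the existing 5 years from the safety visit, which takes completers to about 83 months. If the clock stays at the safety visit, limit the OS comparison to 60 months from first treatment, because beyond that the censoring time again depends on when a patient progressed.
4. Reconcile MRD: make the reporting horizon in 10.2.3, the sampling schedule in Section 7 and Appendix 8, and the statement in 4.1 agree, and replace the randomization clock in 4.1.
5. If only 2 years is feasible, delete the 5-year PFS and MRD analyses and truncate OS and PFS at a common time from first dose that all patients can reach. Someone who stops right after the first dose is followed for 0.9 + 24 = 24.9 months, so that time is about 2 years.

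Cost: an amendment and some extra 3-monthly phone contacts, which the protocol already allows, in a trial of 45 patients. Extending MRD sampling would add marrow samples; shortening the MRD reporting horizon, like option 5, changes wording only.

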## **6.7 Safety Considerations & Supportive Care**

Supportive measures for optimal medical care shall be provided during participation in this clinical trial. Supportive care including anti-nausea / anti-emetic therapy, acid suppression (proton pump inhibitors and/or H2-blockers), glucocorticoids, and other standard treatments may be administered as per institutional guidelines for symptomatic patients. As needed and per individual study site institutional guidelines, prophylactic therapies, including antivirals, antifungals, and antibiotics, may be administered to ameliorate risks associated with non-malignant disorders or of immune system compromise.

### **6.7.1 First Dose Effect (Carfilzomib)**

A “first dose effect” has been seen, which is notable for fever, chills, rigors, and/or dyspnea occurring during the evening following the first day of infusion and an increase in creatinine on Day 2, which may be the clinical sequelae of rapid tumor lysis and/or cytokine release.

All subjects should be well hydrated [Section 6.2.1](#). Clinically-significant electrolyte abnormalities should be corrected prior to dosing with carfilzomib. Renal function must be monitored closely during treatment.

Should a “first dose” effect occur at any point during Cycle 1 or 2, treatment with high dose glucocorticoids (e.g. methylprednisolone 50–100 mg) is recommended. In addition, intravenous fluids,

vasopressors, oxygen, bronchodilators, and acetaminophen should be available for immediate use and instituted, as medically indicated.

### **6.7.2 Safety Information for Carfilzomib**

#### **Hepatitis B Virus Reactivation**

Cases of Hepatitis B Virus (HBV) reactivation have been reported in patients receiving Kyprolis.

Patients should be tested for HBV infection before initiating treatment. For patients who are carriers of HBV, prophylaxis with antivirals should be considered. Carriers of HBV who require treatment with Kyprolis should be closely monitored for signs and symptoms of active HBV infection throughout treatment and following the end of treatment.

Consider consulting a specialist for patients who test positive for HBV infection prior to or during treatment. The safety of resuming Kyprolis after HBV reactivation is adequately controlled is not known. Therefore, prescribers should weigh the risks and benefits when considering resumption of therapy in this situation.

#### **Progressive Multifocal Leukoencephalopathy**

Cases of Progressive Multifocal Leukoencephalopathy (PML) have been reported in patients treated with Kyprolis who have had prior or concurrent immunosuppressive therapy. The casual relationship with Kyprolis is unknown.

Patients should be monitored for any new or worsening neurologic, cognitive or behavioral signs or symptoms that may be suggestive of PML as part of the differential diagnosis of CNS disorders.

If PML is suspected, patients should be promptly referred to a specialist and appropriate diagnostic testing should be initiated. Discontinue Kyprolis if PML diagnosis is confirmed.

### **6.7.3 Tumor Lysis Syndrome (TLS)**

TLS, which may be associated with multi-organ failure, has been observed in treatment Cycles 1 and 2 in some patients with MM who have been treated with carfilzomib. All subjects should follow the hydration

guidelines outlined in [Section 6.2.1](#). If subjects are considered to be at risk for TLS, hydration should be continued into Cycle 2 if clinically indicated.

MM subjects with high tumor burden (e.g., Durie-Salmon or ISS Stage II/III), rapidly increasing M-protein or light chains, or compromised renal function ( $\text{CrCl} < 50 \text{ mL/min}$ ) should be considered to be at particularly high risk.

During Cycles 1 and 2, serum electrolytes and chemistries are closely monitored as outlined in Section 7.1.2. Subjects with laboratory abnormalities consistent with lysis of tumor cells (e.g. serum creatinine  $\geq 50\%$  increase, LDH  $\geq 2$ -fold increase, uric acid  $\geq 50\%$  increase, phosphate  $\geq 50\%$  increase, potassium  $\geq 30\%$  increase, calcium  $\geq 20\%$  decrease) prior to dosing should not receive the scheduled dose. Subjects with such abnormalities should be re-evaluated as clinically indicated. The Lead Principal Investigator should be consulted if there are further delays.

If TLS occurs, cardiac rhythm, fluid, and serial laboratory monitoring should be instituted. Correct electrolyte abnormalities, monitor renal function and fluid balance, and administer therapeutic and supportive care, including dialysis, as clinically indicated.

All cases of TLS must be reported to the Lead Principal Investigator (who will, in turn be responsible for distributing this information to all sites) and to Amgen as a Serious Adverse Event (SAE) through the normal process within 24 hours of the clinical site becoming aware of the event.

#### **6.7.4 Renal Function**

Carfilzomib has not been fully characterized in subjects with creatinine clearance  $< 30 \text{ mL/min}$ . It is critical that the subject's renal function is known at the time of dosing. Renal function, serum creatinine, and serum uric acid should be monitored closely during treatment with carfilzomib. Renal function must be monitored closely during treatment with carfilzomib. Serum chemistry values, including creatinine, must be obtained and reviewed prior to each dose of carfilzomib during Cycles 1 and 2. Refer to [Table 6-8](#) for guidance regarding dose reduction in subjects with compromised renal function.

### **7 SAMPLES FOR MRD EVALUATION AND CORRELATIVE SAMPLES**

Bone marrow samples for MRD evaluation are required and as per the standard of care and will be collected prior to initiation of any MM treatment (pre-induction), screening, at the completion of 8 cycles

of D-KRD, at 24 months and then yearly, or at the time of progression/relapse for up to 2 years. If a CR is suspected after Cycle 8, a bone marrow biopsy and MRD testing will be completed at Cycle 12.

Additionally, provided that the patient consents, correlative samples will be collected and banked for further research studies.

| MRD sample                                                                                | Correlative Sample | Time Points                                                                                                                                                                                                                                                                                                              |
|--------------------------------------------------------------------------------------------------|---------------------------|---------------------------------------------------------------------------------------------------------------------------------------------------------------------------------------------------------------------------------------------------------------------------------------------------------------------------------|
| Bone Marrow Aspirate (MRD samples) or FFPE/BMA slides (ID/calibration sample from pre-treatment) | Bone Marrow Aspirate      | Pre-treatment (calibration sample for MRD only), screening, at end of 8, and 24 cycles, or EOT, yearly after EOT up to 2 years, and at the time of complete response (if applicable: If a CR is suspected after cycle 8, a bone marrow biopsy and MRD testing will be completed at cycle 12 to confirm.)
Progression/Relapse |
|                                                                                                  | Peripheral Blood          | Screening, at end of 8 and 24 cycles or EOT, yearly after EOT up to 2 years, and at the time of complete response (if applicable; If a CR is suspected after cycle 8, a bone marrow biopsy and MRD testing will be completed at cycle 12 to confirm)
Progression/Relapse*                                                    |
|                                                                                                  | Plasma/Serum              | Screening, at end of 8 and 24 cycles or EOT, yearly after EOT up to 2 years, and at the time of complete response (if applicable; If a CR is suspected after cycle 8, a bone marrow biopsy and MRD testing will be completed at cycle 12 to confirm).
Progression/Relapse                                                    |
|                                                                                                  | Buccal Swab               | Screening only                                                                                                                                                                                                                                                                                                                  |

\*Correlative samples only

All bone marrow procedures (including those performed at screening, response and/or progression/relapse) are considered standard of care and a subject may give consent to have extra research samples collected at these visits.

